#### Primary outcomes

Primary outcomes include an improvement in risk factor control status (BP < 140/90 mmHg and fasting blood glucose < 110 mg/dL) and abstinence from smoking or tobacco use.

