### Statistical analysis

Data will be analysed on the basis of the intention to treat principle. Changes observed from the baseline and at follow-up will be compared between the intervention and usual care groups. All data will be de-identified using a unique ID to ensure the confidentiality of information. Upon implementation of the intervention, follow-up measurements will be taken at 6 and 12 months from the baseline. Data will be generated from standardised questionnaires and assessment procedures. Baseline characteristics will be described using means (with standard deviations) or frequencies based on the type of variable. The mean difference between the groups will be examined to understand the effects of the intervention. Mixed effect analysis of covariance will be employed to test for interactions between time (pre and post) and group (intervention or usual care), and partial eta squared (ηp^2^) will be reported as a measure of effect size. The comparisons of variables will be adjusted for potential confounders. The intention-to-treat analysis will be used to observe changes occurred throughout the year during follow-up in participants assigned to the Swāsthya intervention and usual care. The effect attributable to the intervention will be estimated by calculating mean differences between the groups at each of the follow-up points (at the baseline and at 6 and 12 months after the baseline; adjusted odds ratios for dichotomous outcome variables at 95% confidence intervals). Precautions will be taken to rule out the potential interaction effects between the Swāsthya and usual care groups. Software-assisted multiple imputation methods up to five times will be used to deal with missing values. All statistical analyses will be performed using STATA-14 and R software. The effectiveness of the intervention model will be ascertained 1 year after the completion of the study, and the model in itself will also be made public. Information on the study will be available on the website of the college as well as reported in scientific journals and at scientific conferences.

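### The time-by-group test treats baseline as a response: for continuous outcomes, covariates entered only as main effects would not adjust it, and conditioning on baseline would usually use the data better

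*Protocol article*

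**What the plan says.** All of this is in the protocol article, mostly under Statistical analysis.

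- Contrast: "Changes observed from the baseline and at follow-up will be compared between the intervention and usual care groups".
- Named test: "Mixed effect analysis of covariance will be employed to test for interactions between time (pre and post) and group (intervention or usual care"; partial eta squared is its effect size.
- Adjustment: "The comparisons of variables will be adjusted for potential confounders". The text does not say whether covariates act on the level of the outcome, on its change, or both, and nowhere makes the baseline value a regressor.
- A second estimator: "The effect attributable to the intervention will be estimated by calculating mean differences between the groups at each of the follow-up points", with "adjusted odds ratios for dichotomous outcome variables at 95% confidence intervals".
- Missing data: "Software-assisted multiple imputation methods up to five times will be used to deal with missing values", so each analysed data set is complete.
- Visits: "follow-up measurements will be taken at 6 and 12 months from the baseline".

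Under Primary outcomes, the endpoints are an "improvement in risk factor control status (BP < 140/90 mmHg and fasting blood glucose < 110 mg/dL) and abstinence from smoking or tobacco use", which are yes/no statuses. Under Study design and setting, ten ASHA workers and their wards are randomised, five to each arm.

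**The concern.** With pre and post as the two levels of time, the group-by-time term is a contrast of within-person changes. A characteristic that is fixed over time and enters as a main effect shifts both measurements equally and drops out of that contrast. A reader of the section would take the interaction to be confounder-adjusted, and in that form of the model it would not be.

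This matters more than usual because only ten wards are randomised. Chance imbalance in factors that predict later change is likely, and it is what adjustment should address. Conditioning on baseline also generally uses the same measurements more efficiently than a change contrast does.

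**Working it through.** The plan gives no figure on this point to reproduce. Its design inputs are 1452 participants (Sample size) and ten wards, so m = 1452/10 = 145.2 per ward. All correlations and simulated values below are assumptions.

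**Algebra.** Let g be arm, x a time-constant covariate and b a person effect.

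- Pre: y0 = a + γg + δx + b + e0
- Post: y1 = a + τ + (γ + θ)g + δx + b + e1
- Change: y1 − y0 = τ + θg + (e1 − e0)

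δ has gone, so with complete data the estimate of θ is the raw difference in mean change. If x has coefficients δ0 and δ1 at the two visits, the change contains (δ1 − δ0)x and θ is adjusted.

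**Numerical check.** One simulated continuous data set: 10 wards of 145, true effect −0.2, covariate 0.3 SD higher in the intervention arm, covariate coefficient 0.5 before and 0.2 after. The imbalance should therefore move the raw contrast by (0.2 − 0.5) × 0.3 = −0.09. The mixed models had a person random intercept only.

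| Model | Time-by-group estimate |
|---|---|
| Raw difference of mean changes | −0.421158 |
| Time × group | −0.421158 |
| + covariate main effect | −0.421158 |
| + covariate and baseline main effects | −0.421158 |
| + covariate by time | −0.343875 |
| + covariate and baseline, both by time | −0.475591 |
| Follow-up on arm, baseline and covariate | −0.475591 |

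A second simulated ten-ward data set gave 0.17399 with and without the covariate, under either a ward or a person random intercept. Covariate-by-time moved it to 0.0902.

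**Where the identity fails.**

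- Follow-up values missing and not imputed: −0.1260 becomes −0.1280 with the covariate.
- Binary outcome, pre/post logistic GEE: log odds ratio 0.228 becomes 0.238.
- Arm difference at follow-up: −0.564 becomes −0.610 with the covariate, and −0.476 with covariate and baseline.

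**Precision, ward-level linear case.** The variance factors are 2(1 − ρ) for change and 1 − ρ² for baseline regression, so the SE ratio (regression to change) is √((1 + ρ)/2). Here ρ is the correlation of ward means over time:

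ρ = [ICC × CAC + (1 − ICC) r/m] / [ICC + (1 − ICC)/m]

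Assumed ranges: ICC 0.01–0.05, ward autocorrelation (CAC) 0.5–0.9, patient correlation r 0.4–0.6.

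- Lowest ρ (0.01, 0.5, 0.4): 0.007727/0.016818 = 0.459. SE ratio 0.854, or 14.6% smaller.
- Highest ρ (0.05, 0.9, 0.6): 0.048926/0.056543 = 0.865. SE ratio 0.966, or 3.4% smaller.
- Moving from 8 to 7 degrees of freedom multiplies the interval by 2.365/2.306 = 1.025. The CI ratios are 0.876 and 0.990, so 12.4% and 1.0% shorter.

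Read the other way, the change contrast has an SE 1/0.966 to 1/0.854, about 4–17%, larger.

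These factors treat the slope as known. If it is estimated from ten ward means, the expected variance rises by a further 1 + 1/(10 − 4) = 1.167, or 1.080 on the SE scale. The CI ratios become 0.876 × 1.080 = 0.946 and 0.990 × 1.080 = 1.069. The gain survives at low ρ and disappears at high ρ.

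**The case against.** A reader might infer that the trial's main test is unadjusted and that the promise of adjustment is empty. The documents do not support that, for four reasons.

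- The section does not say that covariates enter only as main effects. In the multivariate form of repeated-measures ANCOVA, between-person covariates apply to every within-person contrast, so the interaction is adjusted. Reporting partial eta squared is compatible with that form.
- The interaction is never called the main analysis. The same section estimates arm differences at the follow-up points, and covariates alter those.
- The primary outcomes are binary and take adjusted odds ratios. The exact identity and the SE formulas are linear-model results.
- A difference in change is a valid analysis and, under randomisation, unbiased on average. The simulated shifts illustrate the algebra; they do not estimate bias in this trial.

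All four stand, and they make the point conditional. It might also be said that the covariate list and model terms belong in an analysis plan that is not shown. That holds for the list, whose absence is no finding. It does not dispose of the rest: the article itself chooses a contrast with baseline as a response, and how far the promised adjustment reaches that contrast depends on a model form it leaves open.

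**Conclusion.** The point holds conditionally. For continuous outcomes such as blood pressure, glucose or depression and anxiety scores, with complete or imputed data, the named interaction equals the raw difference in mean change if covariates enter as main effects only. Adjustment then has no effect on it. That part is algebra and needs no assumed figure.

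The precision part is modest and rests on assumed correlations: an SE about 3–15% smaller for baseline regression, and a CI 1–12% shorter after the lost degree of freedom. If the slope is estimated from ward means, the upper end falls to about 5% and the lower end vanishes. None of these figures applies to the binary primary outcomes. This is a low-cost improvement to the stated analysis, not a demonstration that the planned result would be invalid.

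**What to change.** Make the effect estimate the arm difference at 6 and at 12 months, from a model that:

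- includes the participant's own baseline value (for binary outcomes, baseline status in the adjusted odds-ratio model);
- includes prespecified baseline covariates, with visit-specific coefficients for these and for baseline;
- accounts for ward.

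A longitudinal model with equal baseline means in the two arms and covariate-by-visit terms, also accounting for ward, is an alternative. State that the time-by-group term of a main-effects ANCOVA will not be relied on as the test of effect.

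The change is to analysis wording only and uses baseline values already planned. A ward-level analysis gives up one or two error degrees of freedom, plus the slope-estimation cost shown above. With ten wards, covariates should therefore be few and adjusted at participant level where possible.

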Two levels of randomization will be employed in this study. Of the 10 ASHAs, 5 will be randomly allocated either to the treatment intervention arm (Swasthya intervention) or the usual care arm (no interventions other than detailed assessments). Computer-generated random numbers generated by an independent person who is not involved in the study will carry out the randomization of the ASHA workers to either group. Randomization of ASHAs and their clusters will be performed only after the collection of complete baseline data. Their assigned wards will be considered as intervention clusters for the current trial. To eliminate the possibility of contamination, these two groups of ASHA workers will be given training and orientation separately and each of them will be concealed by the group to which they belonged. Independent persons will do the outcome assessment and manage the data to ensure blinding to the Intervention content and its processes. The data analysts will receive the data only after locking the database.

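### Baseline is listed as a time point for the intervention effect although wards are randomised after baseline, and the plan does not say which of its three estimators is the effect estimate

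*Protocol article*

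**What the plan says.** All but one of the statements below are in the Statistical analysis section of the protocol article.

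- **Effect estimate:** the section defines it as "calculating mean differences between the groups at each of the follow-up points (at the baseline and at 6 and 12 months after the baseline". For dichotomous outcomes the same bracket substitutes odds ratios, described as adjusted, with 95% confidence intervals.
- **Follow-up, earlier in the same section:** "Upon implementation of the intervention, follow-up measurements will be taken at 6 and 12 months from the baseline".
- **Change:** "Changes observed from the baseline and at follow-up will be compared between the intervention and usual care groups".
- **Model:** "Mixed effect analysis of covariance will be employed to test for interactions between time (pre and post) and group (intervention or usual care"), with partial eta squared as the effect size.
- **Adjustment:** "The comparisons of variables will be adjusted for potential confounders". No confounders are listed.

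The Study design and setting section fixes the order of events: "Randomization of ASHAs and their clusters will be performed only after the collection of complete baseline data". Five of the ten ASHA wards go to each arm.

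**The concern.** An effect of the intervention cannot exist before anyone has been allocated to it. A between-arm comparison at baseline shows only how evenly a random split of ten wards fell out. Listing it among the effect estimates gives chance imbalance the wrong label. It also contradicts the same section, which places follow-up at 6 and 12 months.

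The second problem is which estimate counts. A raw difference at a visit, a difference in change from baseline and a time-by-group interaction will generally give different numbers in the same data. Only the visit-by-visit sentence says how the effect will be estimated. The interaction is described as a test, and the change sentence as a comparison. Two analysts could each follow the section faithfully and report different results. With five wards per arm, baseline gaps large enough to matter are ordinary.

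**Working it through.** The plan gives no figure on this point to reproduce. It states no ICC, no between-visit correlation and no expected control rate, so every size below rests on assumptions.

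**Inputs.** From the document: 5 wards per arm and 726 patients per arm, so m = 726/5 ≈ 145 per ward. Assumed: 40% controlled at baseline, ICC 0.01 to 0.05, ward-level correlation between visits 0.6 to 0.9, individual-level correlation 0.4.

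**Step 1: size of the chance baseline gap.** SD = √[2·p(1−p)·DEFF/(5m)], with DEFF = 1 + (m−1)·ICC.

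- ICC 0.01: DEFF = 2.44; √(0.48 × 2.44/725) = 4.0 points
- ICC 0.03: DEFF = 5.32; √(0.48 × 5.32/725) = 5.9 points
- ICC 0.05: DEFF = 8.20; √(0.48 × 8.20/725) = 7.4 points

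**Step 2: share of that gap expected in a raw follow-up difference.** The share equals the between-visit correlation of ward means, r = [ICC·ρ_ward + ((1−ICC)/m)·0.4] / [ICC + (1−ICC)/m]. At ICC 0.03, (1−ICC)/m = 0.97/145 = 0.00669.

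- ρ_ward 0.6: (0.0180 + 0.0027)/0.0367 = 0.56
- ρ_ward 0.8: (0.0240 + 0.0027)/0.0367 = 0.73
- ρ_ward 0.9: (0.0270 + 0.0027)/0.0367 = 0.81

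A one-SD gap of 5.9 points would therefore put about 3.3, 4.3 or 4.8 points into the raw 6- or 12-month difference.

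**Step 3: error rates with no true effect.** Ward means were simulated and tested with ward-level t-tests on 8 df, 20,000 trials per setting, over nine combinations of ICC and ward correlation.

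- The raw 12-month test rejects about 5% of the time in all nine settings, so its overall error rate is correct.
- Among trials with a baseline gap beyond one SD, it rejects about 8% to 14% of the time. Adjusted for the baseline ward mean, the figure is about 4% to 5.5%.
- At least one of the 6- and 12-month tests is significant in 7.9% to 9.2% of trials. Counting baseline as a third effect raises this to 10.0% to 12.8%.

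**Step 4: power at 12 months.** True gain 12 points, ICC 0.03, same simulation:

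| Ward correlation | Raw difference | Change from baseline | Adjusted for baseline ward mean (7 df) |
|---|---|---|---|
| 0.6 | 43% | 48% | 51% |
| 0.8 | 43% | 67% | 66% |
| 0.9 | 42% | 82% | 79% |

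The raw difference loses 8, 23 and 37 points against the adjusted analysis. Against the same adjusted analysis, change from baseline is 3 points lower, then 1 and 3 points higher. In a separate run of 6,000 trials per setting, the raw-versus-adjusted loss is 6, 13 and 17 points at ICC 0.01 (74.0/74.8/74.1% against 79.9/87.4/90.7%). At ICC 0.05 it is 7, 22 and 39 points (29.6/30.9/30.5% against 36.6/52.6/69.3%).

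**The case against.** The strongest reply is that the bracket is loose wording for a three-visit table by arm. The section says elsewhere that follow-up is at 6 and 12 months and that baseline characteristics will be described, and no sentence says efficacy will be claimed from baseline. That is plausible, but the sentence as written still defines an effect at a point where none can exist.

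A reader might go further and infer that the 6- and 12-month results necessarily carry the baseline imbalance and are biased by it. The document does not support that. It also plans change from baseline, a time-by-group model and confounder adjustment, and the odds ratios are described as adjusted. Any of these could remove or reduce the imbalance. The confounder list, which might include the baseline outcome, may properly be left to a fuller plan. Under randomisation the gap is chance in either direction, and the unconditional error rate stays near 5%. The 8% to 14% figure arises only by selecting trials with large gaps. Most of the excess in the any-of-three figure is ordinary multiplicity of two follow-up visits; baseline adds about 2 to 4 points.

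It is also fair to say that a baseline-adjusted estimate and a change score are different estimators. Adding the first without rewording the second would leave the conflict in place.

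**Conclusion.** The point holds in limited form. Baseline is wrongly counted as a time point for the intervention effect. The section also offers three estimators without naming the effect estimate or the baseline outcome as a covariate. This is a stated definition that contradicts the design, not a detail left to an analysis plan.

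The consequence depends on which sentence governs. If the visit-by-visit difference does, follow-up estimates include chance imbalance and power is lost: about 6 to 39 points for a 12-point gain over the assumed ICCs and correlations, least when both are low. If change from baseline governs, the loss at ICC 0.03 is at most about 3 points. These sizes rest on assumed inputs and on ward-level analysis of normally distributed ward means; an individual-level odds-ratio model was not simulated. The point is worth correcting because the correction is nearly free, but it does not threaten the validity of the trial.

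**What to change.** In the Statistical analysis section:

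1. Delete baseline from the points at which the intervention effect is estimated, and report baseline values descriptively by arm.
2. Name one effect estimate: the between-arm difference, or odds ratio for dichotomous outcomes, adjusted for the baseline value of that outcome, in a model that accounts for ward.
3. Apply it at each follow-up visit where the outcome is scheduled. By Table 1, that is 6 and 12 months for blood pressure and glucose, and 12 months only for tobacco use.
4. Reword the change-from-baseline and time-by-group sentences so that they describe this estimate or are marked as supportive.

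The glucose adjustment needs one matching clarification: Primary outcomes defines control on fasting glucose, while Study outcomes describes a random measurement. The two must be reconciled so that the baseline covariate and the outcome are the same quantity.

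The cost is wording, plus about one ward-level degree of freedom (7 instead of 8) if the ward mean is also adjusted for. That degree of freedom is already counted in the adjusted power figures. No new visit is needed, since Table 1 schedules baseline blood pressure, blood sugar and tobacco use.

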### Sample size

In the community, 36.33% people aged more than 30 years were found to have HTN and/or DM [9]. Thus, this cluster RCT will include 1452 participants and their families (726 patients in each arm). Trained and certified project staff will collect baseline data by using study questionnaires. Project staff, under the supervision of the principal investigator, will complete data entry into computer systems. The data will be collated, cleaned, and analysed centrally. Furthermore, the accuracy of data entry in randomly selected fields will be independently checked by the principal investigator of the study.

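### The plan caps multiple imputation at five, so a result near the 5% threshold depends more on the random seed than it need

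*Protocol article*

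**What the plan says.** The protocol article has one sentence on missing data, in Statistical analysis: "Software-assisted multiple imputation methods up to five times will be used to deal with missing values". It gives an upper limit and no lower one. It states no expected missing fraction, no seed and no imputation model.

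The same section plans a mixed model: "Mixed effect analysis of covariance will be employed to test for interactions between time (pre and post) and group (intervention or usual care"). It also plans "adjusted odds ratios for dichotomous outcome variables at 95% confidence intervals", which implies a two-sided 5% level. Study design and setting makes ten ASHA wards the randomised units: "Of the 10 ASHAs, 5 will be randomly allocated either to the treatment intervention arm" or to usual care, and "Their assigned wards will be considered as intervention clusters for the current trial". Sample size gives the numbers: "this cluster RCT will include 1452 participants and their families (726 patients in each arm").

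**The concern.** Multiple imputation draws random values, so the pooled estimate carries simulation error that shrinks only as the number of imputations, m, grows. With a small m, two analysts who use the same data, model and code but different seeds get different estimates and p-values. For a result near 5%, that difference can decide whether it is reported as significant. A small m also lengthens the confidence interval.

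Missing follow-up is plausible here. Outcomes are collected through household contact at 6 and 12 months, and participants may withdraw at any time. A ceiling is also the wrong kind of limit: an analyst who used two imputations would comply, and one who used fifty would depart from the plan. Because m and the seed are both left open below the ceiling, the reported result is harder to reproduce than it need be.

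**Working it through.** **No figure to reproduce.** The article states no efficiency, Monte Carlo error or missing fraction for the imputation.

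**Inputs.** From the article: m at most 5; two-sided 5% level, implied by the 95% intervals; 10 wards; 1452 patients, so 1452/10 = 145.2 per ward. Assumed: FMI of 0.05, 0.1 and 0.3.

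**Step 1: which FMI is plausible for the arm effect.** In a ward-randomised trial, variation between wards limits precision, so missing individuals cost less information than their share suggests. Take the variance of a ward mean as ICC + (1 − ICC)/n and suppose 30% of outcomes are missing (n falls from 145.2 to 101.6). Then FMI is about 1 − (complete-data variance)/(observed-data variance). The ICC and the 30% are assumptions.
- ICC 0.01: 1 − 0.01682/0.01974 = 0.15
- ICC 0.02: 1 − 0.02675/0.02964 = 0.10
- ICC 0.05: 1 − 0.05654/0.05935 = 0.05

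An FMI of 0.05 to 0.15 therefore fits this design. An FMI of 0.3 is kept as a pessimistic case.

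**Step 2: seed dependence.** In units of its standard error, the pooled estimate varies over seeds with SD = √(FMI/m). For a result at z = 1.96, the central 95% of seeds gives z = 1.96 ± 1.96 × SD, converted to two-sided normal p-values.

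| FMI | m | SD | z range | p range |
|---|---|---|---|---|
| 0.05 | 5 | 0.100 | 1.764 to 2.156 | 0.031 to 0.078 |
| 0.05 | 50 | 0.032 | 1.898 to 2.022 | 0.043 to 0.058 |
| 0.1 | 5 | 0.141 | 1.683 to 2.237 | 0.025 to 0.092 |
| 0.1 | 50 | 0.045 | 1.872 to 2.048 | 0.041 to 0.061 |
| 0.3 | 5 | 0.245 | 1.480 to 2.440 | 0.015 to 0.139 |
| 0.3 | 50 | 0.077 | 1.808 to 2.112 | 0.035 to 0.071 |

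These ranges are on the narrow side, because the formula holds the estimated variance fixed. A simulation that also let the between-imputation variance and the degrees of freedom vary gave 0.024 to 0.106 at FMI 0.1 and 0.011 to 0.201 at FMI 0.3, both with m = 5.

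**Step 3: interval width.** Set the variance with unlimited imputations to 1. Then T = (1 − FMI) + (1 + 1/m) × FMI, λ = (1 + 1/m) × FMI/T, and df = (m − 1)/λ². The width relative to unlimited m is t(0.975, df) × √T/1.96. At m = 5:
- FMI 0.05: T = 1.010, df = 1133, ratio 1.006
- FMI 0.1: T = 1.020, df = 289, ratio 1.014
- FMI 0.3: T = 1.060, df = 34.7, t = 2.031, ratio 1.067

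Ten wards in two arms leave 8 complete-data degrees of freedom. With the Barnard-Rubin adjustment for 8, the ratios become 1.009, 1.020 and 1.099. At m = 50 and FMI 0.3 the excess is 0.5% (large df) or 0.8% (8 df).

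**Step 4: what the ceiling also permits.** At m = 2 and FMI 0.1: T = 1.05, λ = 0.15/1.05 = 0.143, df = 1/0.143² = 49, t = 2.010. The ratio is 2.010 × √1.05/1.96 = 1.05, so the interval is 5% wider (large df).

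**The case against.** The strongest case against is that five imputations with Rubin's rules are not wrong: the degrees of freedom depend on m and already carry the extra uncertainty, so coverage and type I error are protected. That stands. The relative efficiency, 1/(1 + FMI/m), is 0.98 at FMI 0.1 and 0.94 at FMI 0.3. For this design the lower FMI values are the more plausible ones, and there the loss of width is small. That stands too. But relative efficiency does not measure whether a second run would give the same p-value, and step 2 shows appreciable movement even at FMI 0.05 to 0.1.

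It is also fair to say that step 2 places the result exactly at p = 0.05, where any simulation noise crosses the line. A reader might infer that two analysts would generally reach opposite conclusions. The calculation does not support that. With z = 2.5 and FMI 0.1, the simulation put 99.6% of seeds below 0.05 at m = 5.

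A second tempting inference is that the plan ignores wards when imputing, because the sentence names no ward term. The article does not describe the imputation model at all. An article commonly leaves that to the full protocol or analysis plan, so its silence does not show that ward is omitted. That effect would also run the other way: leaving ward out tends to make intervals too narrow, whereas the slight excess width found here comes only from the small m.

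**Conclusion.** The point holds as a minor one, confined to the stated ceiling. The planned inference is valid, but its reproducibility near the 5% threshold is poorer than it need be. In this ward-randomised design, if 30% of outcomes are missing and the ICC lies between 0.01 and 0.05, the FMI for the arm effect is about 0.05 to 0.15. The width cost is then only about 1 to 3%. At FMI 0.15 with large df, for example, T = 1.03, λ = 0.18/1.03 = 0.175, df = 4/0.175² ≈ 131, t = 1.978, and the ratio is 1.978 × √1.03/1.96 = 1.024. Seed dependence is the larger of the two effects, and it matters only for results close to the threshold. FMI, ICC and the missing rate are all assumptions, because the article gives none of them. No error in how wards are handled in the imputation is established.

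**What to change.** In Statistical analysis, replace the ceiling with a minimum: at least as many imputations as the percentage of incomplete cases, for example 20 to 50. Set the seed before the data are unlocked, record it, and report the Monte Carlo error of the pooled estimate and p-value. If a fuller protocol or analysis plan already sets a number, bring the two texts into line. The cost is computing time only, with no burden on participants, ASHA workers or health centres.
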